## Study Procedures

All patients attending the health care facility will be screened for eligibility, those fulfilling the inclusion and exclusion criteria will be invited to participate in the study.

After provision of written informed consent (Annex VIII) a brief questionnaire will be filled out (Annex IX). Information on demographic background, known hypersensitivity against any of the study drugs and G6PD deficiency will be collected together with the results of a brief physical exam. Depending on body weight, a maximum of 5 ml of venous blood and a fingerprick will be collected from all participants upon enrolment. Additional diagnostic procedures are detailed below.

**Table: Maximum amount of venous blood collected on d0 / body weight**

| **Patient’s approximate weight in kilograms** | **Amount (mL)** |
| --- | --- |
| >6 to 7 | 4-5 |
| >7 | 5 |

All participants will be followed daily until day 2 to provide supervised treatment and ensure clinical and parasitological recovery following chloroquine (Pv arm) or artemether-lumefantrine (Pf arm and Pf/Pv arm) treatment.

Thereafter patients (excluding those with severe G6PD deficiency) will be given unsupervised primaquine for 1 dose (Pf arm) or 14 doses (Pv/mix arm) and reviewed again after 7 days (day 9), 14 days (day 16), 21 days (day 23) and 28 days (day 30). All P. vivax and mixed infections will in addition be followed up after 3 and 10 days (day 6 and 12 respectively) to assure the safety of the provided treatment. Any patient developing signs and symptoms indicative of a malarial episode or an adverse event within the follow up period will be asked to re-attend the clinic for an unscheduled visit, where they will be offered clinical management according to local clinic guidelines. A fingerprick will be performed during every follow up and unscheduled visit, 5ml of blood will be collected for every recurring malaria episode (see table below). Information on adverse events will be collected during every visit. Whenever possible a pill count will be performed on day 16.

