### Treatment & sample collection

Patients will receive the following treatment according to national guidelines (Annex II, IV and V) and will be asked to return for follow up:

- **Vivax patients**

CQ (Annex IV) will be administered for three days under direct observation. All patients will be observed for 30 min after drug administration for adverse reactions or vomiting. Any patient who vomits during this observational period will be re-treated with the same dose and observed for an additional 30 min. If the patient vomits the study drug a second time, he or she will receive rescue therapy as defined by the national treatment guidelines (Annex VI).

PQ (Annex V) will be administered unsupervised for 14 days from day 3 – 16.The complete treatment course of PQ will be provided to the patients after completion of schizontocidal treatment. All patients will receive instructions on how to take the drugs and will be asked to return for follow up on, day 6, day 9, day 12, day 16 (at the end of treatment), day 23 and day 30, as well as whenever the patients suffers from signs and symptoms consistent with malaria or an adverse reaction to one of the study drugs. (Annex IX).

- **Falciparum patients:**

AL will be administered twice daily for three days (Annex III). The morning dose will be supervised and the patients given tablets for the evening dose. Whenever supervised treatment is administered, the study patients will be observed for 30 min after drug administration for adverse reactions or vomiting. Any patient who vomits during this observational period will be re-treated with the same dose of medicine and observed for an additional 30 min. If the patient vomits the study drug a second time, he or she will receive rescue therapy (Annex VI). PQ will be given to the patients after schizontocidal treatment is finished and the patients are advised to take the single dose (Annex V) on day 3 unsupervised. All patients will be asked to return for follow up on day 9, day 16, day 23, day 30 and whenever participants suffer from signs and symptoms consistent with malaria or an adverse reaction to one of the study drugs within the follow up period (Annex IX).

- **Patients with mixed infection (Pf and PV):**

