**Table: Treatment, follow up and sample collection schedule *P.f*, *P. vivax* and mixed infections:**

| **Vivax Patients & Patients with mixed infection** | Day 0 | Day 1 | Day 2 | Day 3 | Day 4 | Day 5 | Day 6 | Day 7 | Day 8 | Day 9 | Day 10 | Day 11 | Day 12 | Day 13 | Day 14 | Day 15 | Day 16 | Day 23 | Day 30 | Un-scheduled visit |
| --- | --- | --- | --- | --- | --- | --- | --- | --- | --- | --- | --- | --- | --- | --- | --- | --- | --- | --- | --- | --- |
| FU P.f. patients | X | X | X | (x) |  |  |  |  |  |  |  |  | X |  |  |  | X | X | X |  |
| FU P.v. patients & mixed | X | X | X | (x) |  |  | X |  |  | X |  |  | X |  |  |  | X | X | X |  |
| Consent | X |  | X |  |  |  |  |  |  |  |  |  |  |  |  |  |  |  |  |  |
| Urinary Pregnancy testing (females, 13- 49years) | X |  |  |  |  |  |  |  |  |  |  |  |  |  |  |  |  |  |  |  |
| Capillary Finger Prick | X | X | X |  |  |  |  |  |  | X |  |  |  |  |  |  | X | X | X | X |
| Venous Blood Sample | X |  |  |  |  |  |  |  |  |  |  |  |  |  |  |  |  |  |  | X* |
| Microscopy | X | X | X | (X) |  |  | X |  |  | X |  |  | X |  |  |  | X | X | X | X |
| Hb | X | X | X | (X) |  |  | X |  |  | X |  |  | X |  |  |  | X | X** | X** | X |
| ACT treatment Pf and Pf/Pv | X | X | X |  |  |  |  |  |  |  |  |  |  |  |  |  |  |  |  |  |
| PQ treatment Pf |  |  |  | X |  |  |  |  |  |  |  |  |  |  |  |  |  |  |  |  |
| CQ treatment Pv | X | X | X |  |  |  |  |  |  |  |  |  |  |  |  |  |  |  |  |  |
| PQ treatment Pf and Pf/Pv |  |  |  | X | X | X | X | X | X | X | X | X | X | X | X | X | X |  |  |  |
| Masimo*** |  |  |  |  |  |  |  |  |  |  |  |  |  |  |  |  | X** |  |  | X |
| Pill count |  |  |  |  |  |  |  |  |  |  |  |  |  |  |  |  | X** |  |  |  |
| AE monitoring  *in case of recurrent parasitaemia  ** in Pv and Pf/Pv patients only  ***only in adults and children >2 yearsX | X | X | X |  |  |  |  |  |  | X |  |  |  |  |  |  | X | X | X | X |

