## Efficacy endpoints

- Proportion of patients with any parasitemia on day 1, 2 and 3 after treatment
- Proportion of patients with fever on day 1, 2 and 3 after treatment
- Recurrence of parasitaemia within 30 days of follow up
- Proportion of Pf patients with gametocytemia on any of the follow up dates.

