# Statistical analyses

- Safety data will be presented as summary statistics (including number, mean, median, interquartile range, standard deviation, minimum and maximum) of all vital signs variables (values and changes from baseline) will be calculated for each visit by treatment group.
- G6PD activity will be categorised and the relative risk (RR) of a drop of Hb > 25% between day 3 and 9 and day 3 and 16 and day 23 and 30 will be calculated per category for all participants treated with 14 days of PQ.
- Hematological results will be presented as continuous variable of Hb concentration at Day 0, 3, 6, 9, 12 and 16. The fractional fall in Hb between baseline and day 9 and 16, will be calculated, as well as the proportion of patients with anaemia less than 7g/dl between day 3 and day 9.
- Parasite clearance rate will be defined according to the World Wide Antimalarial Resistance Network guidelines (WWARN)[[20](#_ENREF_20)]. The parasite clearance time (PCT) is defined as the time elapsed between the patient’s first dose and the time of the first negative blood slide.
- G6PD variants detected will be presented descriptively, G6PD activity observed will be displayed in the form of a histogram displaying G6PD activity vs. number of patients.

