**Early treatment failure**

• Danger signs or severe malaria on day 1, 2 or 3 in the presence of peripheral parasitaemia;

• Parasitaemia on day 2 higher than on day 0, irrespective of axillary temperature;

• Parasitaemia on day 3 with axillary temperature ≥ 37.5 ºC;

• Parasitaemia on day 3 ≥ 25% of count on day 0.

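### Day 3 is undefined as a visit, yet day-3 haemoglobin is the reference for the haemolysis relative risk and other measures also need day-3 values

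*Protocol*

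**What the plan says.** Section 4.4 (Study Procedures) states: "All participants will be followed daily until day 2 to provide supervised treatment and ensure clinical and parasitological recovery". After that, patients are "reviewed again after 7 days (day 9), 14 days (day 16), 21 days (day 23) and 28 days (day 30"), and vivax and mixed infections "will in addition be followed up after 3 and 10 days (day 6 and 12 respectively"). Section 4.4.1 repeats the return days for each patient group, and none of the lists has day 3. Primaquine starts on day 3 but brings nobody to the clinic: falciparum patients are "advised to take the single dose (Annex V) on day 3 unsupervised", and the 14-day course is also unsupervised.

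The CRF (Annex IX) goes from a Day 2 page, where primaquine is handed over (item 19), directly to a Day 6 page.

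Two places point the other way. The schedule table in Section 4.4.1 brackets day 3, for example "FU P.f. patients | X | X | X | (x"), with the same mark for vivax and mixed follow-up and (X) for microscopy and Hb. Its footnotes explain the asterisks but not the brackets. Section 4.5.1 (Microscopy) plans expert re-reading of slides up to day 3.

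The analysis relies on day 3. Section 7 says: "Hematological results will be presented as continuous variable of Hb concentration at Day 0, 3, 6, 9, 12 and 16". It also defines the relative risk of a Hb drop above 25% over day 3 to 9, day 3 to 16 and day 23 to 30. Section 5.2 lists "Proportion of patients with any parasitemia on day 1, 2 and 3 after treatment" and a matching fever endpoint. Section 5.1 has anaemia below 7 g/dl on days 3 and 9. Annex VII includes "Parasitaemia on day 3 ≥ 25% of count on day 0" among the early-failure criteria.

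**The concern.** The relative risk by G6PD category is the one relative-risk analysis in Section 7, and it serves the secondary objective on haemolysis and G6PD activity. A change measured from just before primaquine separates the effect of the drug from the fall in Hb caused by the malaria episode. The named reference, day-3 Hb, is not reliably collected. Falling back on day 0 would mix pre-treatment change with on-treatment change.

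If the brackets mean that only patients still positive or ill return on day 3 (an assumption, since the protocol does not say), the Hb reference would come from a selected group. A statistical analysis plan could choose another reference day, but it cannot recover slides, temperatures or Hb values that were never taken.

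**Working it through.** The protocol states no figure to reproduce here, and its enrolment target carries no statistical inputs. The check sets each source on collection against each measure that uses day 3.

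**Is day 3 collected?**

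| Source | Day 3 |
| --- | --- |
| Sections 4.4 and 4.4.1, text | Not listed for any patient group |
| Section 4.4.1, schedule table | Bracketed for follow-up, microscopy and Hb; brackets unexplained |
| Section 4.5.1, Microscopy | Slides up to day 3 expected |
| Annex IX, scheduled CRF pages | Days 0, 1, 2, 6, 9, 12, 16, 23, 30; no day 3 |
| Annex IX, unscheduled-visit pages | Could record a day-3 attendance, but only for patients who come back unprompted |

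**What needs day 3?**

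| Measure | Day-3 dependence |
| --- | --- |
| Relative-risk windows (Section 7) | 2 of 3; the third, day 23 to 30, lies after primaquine ends on day 16 |
| Hb series (Section 7) | 1 of 6 time points; day 2, which is collected, is left out |
| Anaemia below 7 g/dl from day 3 to day 9 (Section 7) | Starting point |
| Safety endpoints (Section 5.1) | 1 of 5: anaemia on days 3 and 9 |
| Efficacy endpoints (Section 5.2) | 2 of 4, day-3 part only: parasitaemia and fever |
| Early-failure criteria (Annex VII) | 2 of 4 rest on day 3 alone; a third covers day 1, 2 or 3 |

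Not affected: severe anaemia, transfusion, fractional Hb change from baseline, adverse events, 30-day recurrence, gametocytaemia, parasitaemia and fever on days 1 and 2, the day 23 to 30 window, and the failure criterion comparing day 2 with day 0.

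**How many patients does the relative risk concern?** Section 8 targets about 50 vivax and 160 falciparum cases, 50 + 160 = 210 in all. The relative risk is restricted to 14-day primaquine recipients, so the 160 falciparum cases do not enter. Section 8 gives no target for mixed infections. If they arrive in the 2013 Alikadam ratio of 26 mixed to 142 vivax (an assumption), they add 50 × 26/142 ≈ 9. Patients with severe G6PD deficiency receive no primaquine and drop out of this count; the protocol does not say how many to expect.

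**Is there a usable pre-primaquine value?** Yes. Day-2 Hb is an unbracketed X in the schedule for everyone, has a CRF field (item 15), and precedes the first dose on day 3. Moving the reference lengthens the windows by one day: from 9 − 3 = 6 to 9 − 2 = 7 days, and from 16 − 3 = 13 to 16 − 2 = 14 days.

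**A sequence that does not fit.** The CRF end-of-study form offers early treatment failure before primaquine as a reason for stopping. Primaquine is dispensed on the Day 2 page, so the two criteria resting on day 3 cannot have been assessed by then. Section 4.4.3 ties treatment failure to rescue treatment.

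**The case against.** A reader might infer that no day-3 data will exist and that the main safety, efficacy and failure measures cannot be computed at all. The documents do not support that. The schedule brackets day-3 follow-up, Hb and microscopy, the microscopy section expects slides to day 3, and a day-3 attendance could be entered on an unscheduled-visit page. Most endpoints do not use day 3.

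A reader might also cite the empty day-3 cells in the finger-prick and adverse-event rows. These show nothing specific to day 3: the same rows are empty on days 6 and 12, which are certain visits for vivax and mixed infections.

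Nor is a pre-primaquine Hb lacking. Day-2 Hb is planned for all, so for the relative risk the fault lies in which day Section 7 names.

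Finally, selection need not bias every measure. If positive patients were the ones brought back, the two criteria resting on day 3, which both require parasitaemia, would be checked in those most able to meet them. Selection is plausible for day-3 Hb and perhaps fever. It is not shown for early failure, nor for positivity if all enrolled patients stay in the denominator.

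These points limit the reach of the finding. They do not remove the contradiction: the text and CRF have no day-3 visit, the schedule has one of unknown meaning, and Sections 5 and 7 and Annex VII rely on it.

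**Conclusion.** The protocol is internally inconsistent on day 3 and should be corrected before enrolment. As written, the day-3 components are either uncollected or available only for an undefined, possibly selected subset. The most serious consequence is that both on-treatment windows of the G6PD relative risk, in about 50 vivax patients plus mixed infections, lack a reliably collected reference. The day-3 parts of one anaemia, one parasitaemia and one fever endpoint, and two early-failure criteria (a third in part), have the same weakness. The count rests on reading the visit lists and CRF pages as complete. The selection argument rests on an assumed meaning of the brackets.

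**What to change.** 1. In Section 7, make day-2 Hb the pre-primaquine reference for the relative-risk windows now starting on day 3, and add day 2 to the Hb series. This costs wording only, since the value is already scheduled and on the CRF.
2. For the day-3 anaemia, parasitaemia and fever endpoints in Section 5, the matching Section 7 anaemia proportion and the synopsis, choose one of two routes. Either define day 3 as a visit for all patients, in the procedures text and schedule and with a CRF page, or restate these endpoints on days that are collected. The first costs one short visit and one CRF page; the second costs wording.
3. State what the brackets in the schedule table mean, or remove them.
4. Reconcile the day-3 early-failure criteria in Annex VII, the visit schedule, primaquine dispensing on day 2 and the CRF stopping reason about early failure before primaquine. Because failure leads to rescue treatment, which clinical rule applies is for the investigators to settle; this review proposes none.

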## Hemoglobin

. Haemoglobin (Hb) will also be measured at baseline and on all follow up visits using a Hemocue Hb (Angelholm, Sweden) machine.

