# Assessment of variables and statistical methodology

## Safety endpoints

- Proportion of patients with severe anaemia (Hb<7g/dl)
- Proportion of patients receiving blood transfusion
- Fractional change in Hb between baseline and day 6, 9,12,16, 23 and 30 (incl. proportion of patients with >25% drop in Hb between the timepoints)
- Proportion of patients with anaemia less than 7g/dl on day 3 and day 9
- Proportion of patients with adverse and serious adverse events

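### The undated severe-anaemia proportion is ascertained on unequal Hb schedules in the vivax/mixed and falciparum groups, and the schedule table disagrees with the text on how unequal they are

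*Protocol*

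**What the plan says.** **Visits, by the text.** In Treatment & sample collection (4.4.1), falciparum patients receive PQ after artemether-lumefantrine and "the patients are advised to take the single dose (Annex V) on day 3 unsupervised". Their visits follow: "All patients will be asked to return for follow up on day 9, day 16, day 23, day 30". For vivax and mixed patients PQ "will be administered unsupervised for 14 days from day 3" to day 16. Study Procedures (4.4) adds to the shared days: "All P. vivax and mixed infections will in addition be followed up after 3 and 10 days (day 6 and 12 respectively".

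**What is done at visits, by the text.** The Hemoglobin section (4.5.2) says Hb "will also be measured at baseline and on all follow up visits". On adverse events, 4.4 says: "Information on adverse events will be collected during every visit".

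**Endpoints.** Safety endpoints (5.1) lists "Proportion of patients with severe anaemia (Hb<7g/dl") with no day attached. The adverse and serious adverse event proportion is also undated. Other Hb endpoints in the same list name their days.

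**The schedule table in 4.4.1** differs from this text in three ways:
- The falciparum follow-up row marks day 12 and leaves day 9 blank.
- Hb on days 23 and 30 carries a footnote limiting it to vivax and mixed patients.
- The adverse-event and finger-prick rows leave days 6 and 12 blank, although the Hb row marks both.

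**The concern.** A patient meets the severe-anaemia endpoint only if a measurement falls while Hb is below the threshold. A group measured more often has more chances to meet it at the same true risk. In falciparum patients the text schedules nothing between the day 3 dose and day 9. The day 3 visit itself is bracketed in the table for every group, so it does not offset the gap.

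The primary objective covers PQ side effects in both vivax and falciparum patients. Readers will therefore see a severe-anaemia proportion for each group, one overall figure, or both. Shown side by side, the proportions differ partly because of visit frequency. An overall figure mixes two levels of ascertainment in a ratio set by the case mix, with targets of about 50 vivax and 160 falciparum patients. Sample Size (section 8) says that primary-objective results will be pooled with other sites, so such a figure may travel further than this report.

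The proportion below 7 g/dl that Statistical analyses (section 7) describes as lying between day 3 and day 9 has the same feature if read as a window. By the text, the scheduled looks after day 3 are days 6 and 9 in vivax/mixed patients and day 9 alone in falciparum patients.

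**Working it through.** The plan gives no figure to reproduce here. The enrolment target comes from 2013 caseload and does not enter the ratios below.

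**Step 1. Scheduled Hb checks after PQ starts**

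| Source | Vivax/mixed | Falciparum | Days common to all |
|---|---|---|---|
| Text (4.4, 4.4.1, 4.5.2) | 6, 9, 12, 16, 23, 30 (six) | 9, 16, 23, 30 (four) | 9, 16, 23, 30 |
| Schedule table (follow-up and Hb rows with footnote) | 6, 9, 12, 16, 23, 30 (six) | 12, 16 (two) | 12, 16 |

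**Step 2. Chance that a scheduled visit catches a dip**

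Assumptions, none of them from the protocol: Hb stays below the threshold for w days; onset is uniform over days 3 to 16 (13 days); the true risk is equal in both groups; unscheduled visits are ignored. A visit on day v catches onsets in (v − w, v]. The chance is the length of the union of these intervals within days 3 to 16, divided by 13.

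For w = 2, vivax/mixed visits on days 6, 9, 12 and 16 cover 2 days each, 8/13. Falciparum visits (text) on days 9 and 16 cover 4/13. For w = 5, the vivax/mixed intervals overlap and cover all 13 days, while the falciparum intervals (4, 9] and (11, 16] cover 10.

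| Dip length w | Vivax/mixed | Falciparum, text | Ratio | Falciparum, table | Ratio |
|---|---|---|---|---|---|
| 2 days | 8/13 = 62% | 4/13 = 31% | 2.0 | 4/13 = 31% | 2.0 |
| 3 days | 12/13 = 92% | 6/13 = 46% | 2.0 | 6/13 = 46% | 2.0 |
| 5 days | 13/13 = 100% | 10/13 = 77% | 1.3 | 9/13 = 69% | 1.4 |
| 7 days | 13/13 = 100% | 13/13 = 100% | 1.0 | 11/13 = 85% | 1.2 |

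**Step 3. Sensitivity to onset**

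Falciparum patients take one dose on day 3, so earlier onset is also worth trying. With onset uniform over days 3 to 9 (6 days) and the text schedule:
- w = 2: 4/6 against 2/6, ratio 2.0
- w = 3: 6/6 against 3/6, ratio 2.0
- w = 5: 6/6 against 5/6, ratio 1.2
- w = 7: 6/6 against 6/6, ratio 1.0

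On the table's falciparum days the chances are 0, 0, 2/6 and 4/6.

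**Step 4. An overall proportion**

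With w = 3, onset over days 3 to 16, the text schedule and the enrolment targets (no target is given for mixed infections, so they are left out), the share of dips caught is (50 × 12/13 + 160 × 6/13) / 210 = 120/210 = 57%. On the days common to both groups it is 6/13 = 46% in each, whatever the case mix.

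**The case against.** The strongest reply is that nothing in the protocol compares the groups. The primary objective is to assess side effects. The only relative measure, the relative risk of an Hb drop above 25% by G6PD category, is confined to patients on 14 days of PQ, who share one schedule. The groups also differ in species, in PQ exposure and, for vivax against falciparum, in partner drug, so a contrast would not isolate PQ safety even with equal visits. This stands, and it limits the point to descriptive figures.

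Four stronger readings might be inferred, and the documents do not support them:

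- **That by-group any-visit proportions are already specified.** The phrase "will be calculated for each visit by treatment group" in Statistical analyses concerns vital signs tabulated per visit, and a per-visit table is not distorted by the number of visits. Nor does the protocol say that the groups will be pooled; the pooling in Sample Size is across sites.
- **That single-dose PQ looks safer by construction.** At a 7-day dip the text schedule gives no difference. Unscheduled visits with Hb are open to every group, and signs of severe haemolysis are a listed reason for one (Annex X). The extra visits have a stated safety purpose, and earlier detection could also prevent later severe anaemia. The net direction is not fixed.
- **That adverse events are affected in the same way.** The symptom form records onset and resolution dates, so an event on day 5 can be reported on day 9. What differs is mainly recall. The schedule table also does not mark adverse-event collection on days 6 and 12, against the text.
- **That all Hb endpoints are affected.** Those tied to a named day are comparable on any day that both groups attend.

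It can also be said that the choice of visits feeding a table belongs in the analysis plan. The table rule may well be settled there. The unequal schedule, the undated endpoint and the conflict between text and table are in the protocol itself.

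**Conclusion.** The point holds as a limitation of descriptive figures. Severe anaemia without a time point is ascertained on six scheduled Hb checks in vivax/mixed patients against four in falciparum patients by the text, or two by the table. If proportions are set side by side or merged, the apparent ratio at equal true risk runs from about 2.0 (dips of 2 to 3 days) to 1.0 (7 days) on the text schedule, and from 2.0 to 1.2 on the table. These sizes rest on assumed dip lengths and onset times and leave out unscheduled visits, which would narrow the gap to an extent the documents do not allow one to estimate. No planned test or estimate of a group difference is invalidated, and the extra visits themselves are not at fault.

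The conflict between text and table matters in its own right. Until it is resolved the common Hb days are unknown. If the table's falciparum row governed, that group would have no scheduled day 9 Hb for the endpoints that name day 9.

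**What to change.** 1. Reconcile Study Procedures (4.4), the falciparum paragraph of 4.4.1 and the Hemoglobin section (4.5.2) with the schedule table on two matters: whether the falciparum visit is on day 9 or day 12, and whether falciparum patients have Hb measured on days 23 and 30. Align the adverse-event and finger-prick rows with the text for days 6 and 12. Which version is right is for the investigators.
2. Report the all-visit Hb-threshold proportions within each group. Beside them, add a table of the same proportions by group and overall, restricted to the scheduled days common to all groups plus unscheduled visits. Those days would be 9, 16, 23 and 30 if the text stands, or 12 and 16 if the table stands.
3. Keep adverse and serious adverse events reported in full by onset date, with a note that scheduled visit frequency differed between groups. Events first reported on days 6 or 12 should not be dropped from the main safety figures.

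The cost is a correction to the schedule and one more table from Hb data that the reconciled schedule already collects. The downside is that the common-day figures use less of the vivax/mixed Hb data, which the all-visit proportions retain.
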